### Statistical analysis

#### Sample size consideration

The main objective being to estimate the incidence of occurrence of neurological complications in the cohort, with an expected proportion P varying from 0.2 to 0.5, for a confidence level of 95 %, with alpha risk of 5 %, the number of subjects to be included varies between 246 and 384. Given the risk of relatively early death related to the disease, the inclusion of 400 patients will provide good statistical power for this purpose.

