**Fig. 1 Fig1:**
[figure not shown]
Study procedure

Every 3 months, once the MRI of the patient is done, a medical visit occurs during which a short cognitive assessment is performed (the CSCT).

Cognitive tests, scales and questionnaires used for the formal assessment are listed in Table 2. An extensive evaluation lasting 2 h is performed with a trained neuropsychologist, followed by self-reported and caregiver-reported scales and questionnaires. The explored domains are intellectual efficiency, general functioning, verbal and visual episodic memory, attention, executive functioning, language, visuospatial and visuoconstructive abilities, mood, fatigue, quality-of-live, subjective complaints and autonomy. The formal assessment occurs at baseline and yearly after radiotherapy. In case of CSCT score decrement during follow-up the next yearly formal assessment is performed earlier. CSCT decrement is defined as a loss of 1 standard deviation compared to baseline (given its low learning-effect and good stability in controls [22]), during two consecutive assessments. The necessity of detecting a decrement during two visits permits to insure that a variation in score is not due to a transitory cause like an infection or fatigue, which is reversible and not linked to leukoencephalopathy. This procedure will allow to study the nature, course and incidence of cognitive decrement following radiotherapy in this population. At baseline and during the follow-up, the CSCT will be compared to the formal cognitive assessment to study its sensibility to detect impairments in this context.

**Table 2 Tab2:** Tests and questionnaires used for the cognitive, mood and behavioral assessment

Domain	Tests, scales and questionnaires
Cognitive assessment	
Intellectual efficiency	National Adult Reading Test (French version) [38]
General functioning	Mini Mental State Examination [39]
	Montreal Cognitive Assessment [40]
	Dementia Rating Scale-2 [41]
Verbal episodic memory	RLRI-16 (Adaptation of the Grober-Buschke test) [42]
Visual episodic memory	Rey-Osterrieth Complex Figure [43]
Executive functions and Attention	Digit Span forward [44]
	Digit Span backward [44]
	Letter-number sequencing [44]
	Categorical and phonetic word fluency [45, 46]
	Trail Making Test [45, 46]
	Computerized Speed Cognitive Test [22]
	Stroop color-word Test [45, 46]
Langage	Boston Naming Test [47]
	Token Test [48]
Visuospatial and visuoconstructive functions	Rey-Osterrieth Complex Figure [43]

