#### Planned analysis

The combination of data from four axes (Clinical Epidemiology, Dosimetry, Biomarkers and Radiobiology) will give the opportunity to precisely analyze the links between cognitive impairments and changes in biomarkers depending on the precise dose absorbed at different brain areas during radiotherapy brain cancer.

Descriptive statistics (means, standard deviations, percentages and 95 % confidence intervals) will be used to describe the distribution of subjects according to each of the terms of the variables studied. Analyses of variance to one or more classification criteria will be used to compare the means of continuous quantitative variables. Chi-square test or Fisher exact test will be used to compare the distribution of nominal discrete variables and / or ordinal. All tests will be bilateral with alpha = 5 %. Details of the analyzes are shown below:

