One other important goal of our project is to improve the detection of cognitive defects at early stage. Current formal assessment of cognitive status lasts between 1 and 2 h or more, and cannot be performed as often as needed in this population because of an important learning-effect. The *Compurterised Speed Cognitive Test (CSCT)* is a quick cognitive assessment tool validated in a population of patients presenting multiple sclerosis. The CSCT just need few minutes to be performed and appears to be a potential useful tool in the patient follow-up [36]. This test use in the neuro-oncologic context could importantly improve the detection of cognitive impairments and decrement. Our study will help to validate its use in our population by comparing the CSCT to a more complete battery at baseline time before radiotherapy and during the follow-up after treatment. Several biomarkers of neurotoxicity will be also tested in our population in order to try to individualize prognostic biomarkers of leukoencephalopathy.

Prospective methodology of data collection and the choice of a homogenous population will allow us to analyze precisely the selected outcomes, avoiding potential bias linked to retrospective studies. However, one limit of our study is to focus only on patients with high grade of glioblastoma, who are known to have a very short life expectancy, with a median expected survival being less than 18 months [37]. Nevertheless, it seems that leukoencephalopathy could appear as soon as within the 6 first months after radiotherapy. Furthermore, the rather large number of included patients will allow us to characterize cognitive defects at short and medium term.

With a better screening and understanding of neurotoxicity, the treatment regiments could be adapted to risk factors present for each patient in order to reduce complication. More, preventive actions and cares could be developed to reduce the burden of cognitive deficits and preserve the quality-of-life and autonomy for patient at risk.

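### The 400 planned inclusions are presented as covering early death, but against an unstated ±5-point target they allow only 4% loss at P = 0.5

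*Protocol article*

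**What the plan says.** Under Sample size consideration, the protocol article gives the aim as estimation: "The main objective being to estimate the incidence of occurrence of neurological complications in the cohort". The inputs are "with an expected proportion P varying from 0.2 to 0.5" and "for a confidence level of 95 %, with alpha risk of 5" %, and from these "the number of subjects to be included varies between 246 and 384". The paragraph then refers to early death from the disease and states that "the inclusion of 400 patients will provide good statistical power for this purpose". It gives no interval width, loss rate, hypothesis or power value.

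Four other places bear on this:
- Discussion: short life expectancy is named as a limit of the study, "with a median expected survival being less than 18 months". The same paragraph notes that onset within six months of radiotherapy is possible.
- Procedures: "The formal assessment occurs at baseline and yearly after radiotherapy". It is brought forward if the CSCT falls by one standard deviation at two consecutive three-monthly visits.
- Study endpoints: the endpoint is a decline from baseline in two or more domains, once local recurrence has been excluded.
- Analysis of evaluation criteria: one incidence estimate for the cohort is planned. Whether its denominator is all included patients or those formally assessed is not said.

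**The concern.** A number of subjects for estimating a proportion cannot be obtained without a target width, so the paragraph omits the input that fixes its result. Confidence level and alpha are one quantity given twice. Power has no meaning here, because no hypothesis is tested for the primary objective.

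The more substantial problem is the step from 384 to 400. The text offers it as the answer to early death, but it adds only 16 patients in a disease where the article itself expects over half to die within 18 months. The endpoint needs a formal assessment after radiotherapy, and the first scheduled one is at a year. Patients who die or recur before being assessed supply no endpoint measurement. This paragraph is the only justification given for N on the primary objective, so a reader would credit the incidence estimate with a precision that may not be reached.

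**Working it through.** **Inputs.** P = 0.2 to 0.5, 95% confidence, N = 246 to 384, 400 included (Sample size consideration). Two-sided z = 1.96 ("All tests will be bilateral with alpha = 5" %, Planned analysis). Median survival below 18 months (Discussion). Assumption, not in the document: exponential survival with the median set at its upper bound of 18 months.

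**1. Reproduce the stated numbers.** n = 1.96² × P(1 − P) / d².
- P = 0.2, d = 0.05: 3.8416 × 0.16 / 0.0025 = 245.9, stated as 246.
- P = 0.5, d = 0.05: 3.8416 × 0.25 / 0.0025 = 384.2, stated as 384.

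Half-widths of 3, 4, 6 and 10 points do not give this pair. The stated numbers are therefore correct for d = 5 points. The formula has no attrition term, so they count patients with an observed outcome, although the text calls them subjects to be included.

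**2. Loss that 400 can absorb.**
- At P = 0.5: 1 − 384/400 = 4.0%.
- At P = 0.2: 1 − 246/400 = 38.5%.

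**3. What the median alone implies.** A median below 18 months means that fewer than 200 of 400 are expected alive at 18 months, whatever the shape of the curve. That is below both 246 and 384. With 200, the half-width 1.96 × √(P(1 − P)/n) is 5.5 points at P = 0.2 and 6.9 at P = 0.5, so these are best cases.

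**4. First scheduled formal assessment.** Alive at time t: 400 × 0.5^(t/18). At t = 12 this is 400 × 0.630 = 252.
- P = 0.2: 1.96 × √(0.16/252) = 4.9 points.
- P = 0.5: 1.96 × √(0.25/252) = 6.2 points.

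With 252 patients, 5 points is met only while P(1 − P) ≤ 252 × 0.0025 / 3.8416 = 0.164, that is, for P up to about 0.21. If the median were 12 months, 200 would be alive at 12 months, with half-widths of 5.5 and 6.9. None of this removes patients with local recurrence, for which the document gives no rate.

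**5. The other possible denominator.** Over all 400, the half-width is 1.96 × √(0.16/400) = 3.9 points at P = 0.2 and 1.96 × √(0.25/400) = 4.9 at P = 0.5. This applies to a crude cumulative incidence of observed decline, with death and recurrence as competing events.

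**6. Illustration of later times, same assumption.** 159 alive at 24 months (6.2 to 7.8 points) and 100 at 36 months (7.8 to 9.8 points).

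**The case against.** There is no arithmetic error: both numbers reproduce, and the 5-point width can be recovered from them. An article condenses a fuller protocol, the repeated alpha is only redundant, and the word power is loose usage. This stands as far as it goes: these wording faults change no number. What remains is that the article itself offers 400 as the allowance for early death, and that statement can be checked against its own survival figure.

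Survivors at a date are also not the same as the analysable number. A CSCT decline can bring the formal assessment forward, onset may be early, and a patient who is found to have declined and later dies still contributes. This stands too. It is why the conclusion depends on the incidence measure, and why an estimate over all 400 keeps about 5 points.

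The survival input is imperfect. The median is quoted for glioblastoma without a time origin, whereas Table 1 also admits grade III glioma. The recurrence condition may mean ruling out recurrence as the cause of a decline rather than removing every patient who recurs. These points limit the exact counts. However, the article offers no other survival figure and presents this one as a limit of this study.

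A reader might infer that the plan fails its precision throughout the P range, or that it falls short at 24 and 36 months. The document does not support either inference. At P = 0.2 the 12-month survivors under the base assumption (252) still meet 246, and no separate proportions at 24 or 36 months are planned.

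**Conclusion.** The point holds in a limited form. The step to 400 cannot serve as the allowance for early death across the stated P range: it covers 38.5% loss at P = 0.2 but 4% at P = 0.5, against a median survival below 18 months. If incidence is the proportion among patients formally assessed, the cost at the first yearly assessment is about 6.2 instead of 5 points at P = 0.5, on survival alone and assuming an exponential curve with an 18-month median. The cost is larger if the median is shorter or if patients with recurrence are removed. If incidence is the crude cumulative incidence over all 400, about 4.9 points at P = 0.5 is kept and the claim is acceptable once it is worded as precision. The 24- and 36-month figures are illustrations under the stated assumption, not failures of a planned estimate. The fault lies in the justification of N and does not by itself call for a larger cohort.

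**What to change.** Keep 400 and replace the closing sentence of Sample size consideration with a precision statement that gives:
- the target, a 95% confidence interval half-width of 5 points;
- the incidence measure it applies to, either the crude cumulative incidence over all included patients with death and recurrence as competing events, or the proportion among those formally assessed;
- the assumed loss to death and to recurrence before a formal assessment after radiotherapy, with the time origin of the survival figure;
- the resulting expected half-width. This is about 4.9 points at P = 0.5 for the measure over all 400. For the proportion among those assessed it is about 5 to 6 points at the first yearly assessment on survival alone, and wider after recurrence exclusions or at later times.

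Say precision instead of power, and give the confidence level once. The cost is one rewritten paragraph and, for the proportion among assessed patients, a less favourable stated precision. Enrolment, visit schedule and procedures do not change.

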#### Planned analysis

The combination of data from four axes (Clinical Epidemiology, Dosimetry, Biomarkers and Radiobiology) will give the opportunity to precisely analyze the links between cognitive impairments and changes in biomarkers depending on the precise dose absorbed at different brain areas during radiotherapy brain cancer.

Descriptive statistics (means, standard deviations, percentages and 95 % confidence intervals) will be used to describe the distribution of subjects according to each of the terms of the variables studied. Analyses of variance to one or more classification criteria will be used to compare the means of continuous quantitative variables. Chi-square test or Fisher exact test will be used to compare the distribution of nominal discrete variables and / or ordinal. All tests will be bilateral with alpha = 5 %. Details of the analyzes are shown below:

#### Description of the population at baseline (before radiotherapy)

This description will include:Medical data collected in the questionnaire, including in particular the baseline risk factors of neurological complications.All biomarkersThe MRI abnormalitiesThe results of CSCT and complete cognitive assessments.

The results will be presented for the complete sample.

#### Dose assessment

This reconstruction will be made for each patient based on data from radiotherapy treatment plan. Histograms of dose/volumes will be retrieved for each structures of interest listed in Table 3 in order to study correlations between anatomic regions and neuropsychological dysfunctions.

#### Analysis of evaluation criteria

Based on primary endpoint definition, the estimate of the incidence of cognitive impairment related to radio-induced leukoencephalopathy in our cohort will be made.

An analysis of the dose–response relationship between radiation dose absorbed by different brain structures and cognitive abnormalities observed after radiotherapy will be made using a multivariate Cox model taking into account the delivered dose to the organ of interest and the time occurrence of cognitive complications. An adjustment on risk factors for cognitive complications will be achieved. Similarly for patients with cognitive impairment before radiotherapy, an analysis of potential associated risk factors will be carried out with the use of a multivariate model.

Secondary judgments criteria, including changes in MRI images relative to the reference imaging and changes in series of biological markers between measurements before RT, 4 weeks, 12 month and 36 months after RT, will be analyzed by parametric distribution comparison tests (Z) or nonparametric if needed (Wilcoxon tests).

In addition, an analysis will be conducted of the sensitivity and specificity of the CSCT to demonstrate cognitive impairment by comparing the CSCT performed before radiotherapy and detailed neuropsychological assessment (gold standard) achieved at the same time. More, CSCT decay during follow-up will be analyzed by comparing its results to formal assessment during years after treatment, to study its sensibility in detecting cognitive decrement after radiotherapy.

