From a biological point of view, biological mechanisms of the initiation and progression of cognitive impairements is not well known. However, specific biomarkers predictive of the cognitive impairments in this population would help in screening patients at risk of neurotoxicity. Currently, biomarkers of neurotoxicity have been poorly studied. Thus, several markers deserve to be explored such as the S-100B protein known to be a marker of traumatic cerebral lesion, neurodegenerative diseases and aggressive gliomas [17], specific isoprostanes (as 8,12-*iso*-iPF_2α_-VI) implicated in the oxidative/nitrate stress in neurodegenerative diseases [18] and homocystein which plasma concentration has been associated with poor memory performances in old individuals [19]. Furthermore, new biomarkers seems to be potentially very interesting. Indeed, micro RNA and microparticules have been identified as potential biomarkers of neurological defects [20, 21]. Then the strategy proposed is to test classical and new biomarkers in order to individualize those, which could be accurate for the screening of patients at risk of cognitive impairments.

At last, assessment of cognitive impairment is difficult because the exploration of cognitive side effects is not systematic and often depends on patients’ complaints and clinicians’ sensibility to this aspect. A formal neuropsychological assessment can’t be performed in routine, as often as it should be for an adapted follow-up of brain tumor patients. Indeed, it is time consuming, needs expert professionals and validated material, and consequently it is not easily implemented in most medical center. A new tool for exploration of cognitive deficits is the *Computerized Speed Cognitive Test* (Legal deposit: IDDN.FR.001.180018.000.S.P.2014.000.31230) (CSCT) [22]. The CSCT was first developed to assess information speed processing in multiple sclerosis. Because it presents a low learning-effect and focuses on a cognitive characteristic often impaired in neuro-oncologic population, it could be used to detect a cognitive deterioration during repeated medical visits, and thus be used as an alarm to start a more extensive formal assessment. Then, it is suitable for the follow-up of a cohort of patients treated for brain tumor and allows to give quick and reliable information on cognitive impairment, compatible with the usual clinical follow-up of the patients.

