### Objectives

The purpose of the EpiBrainRad study is to establish a cohort of patients treated with radiotherapy for a high grade glioma.

The main objective is to estimate the cognitive impairment incidence related to radio-induced leukoencephalopathy in this population.

Secondary objectives are:To study the impact of associated risk factors on leukoencephalopathy development, including individual factors and treatment.Biologic markers of neurologic degradation will be studied to evaluate the correlations between cognitive impairments and biological abnormalities.Specific organs dosimetry (such as hippocampus, temporal lobes, corpus callosum, peri-ventricular white matter, posterior fossa) correlated with radiologic abnormalities on magnetic resonance imagery (MRI) and clinical symptoms will be analyzed to better understand the evolution of radio-induced leukoencephalopathy.Finally, the assessment of the sensibility and specificity of a quick cognitive test, *the Computerised Speed Cognitive Test* [22], to detect a cognitive decrement during the follow up of the patients.

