### Study endpoints

The primary endpoint is the reduction in performance on cognitive tests defined as follows: After exclusion of local recurrence, decreased detailed neuropsychological assessment score compared to the patient's baseline score before radiotherapy for at least 2 cognitive domains.

Secondary endpoints are:Differences in biomarkers’ concentration between the measurements before RT and: at the end of the RT, RT + 4 weeks, RT + 12 months and RT + 36 months.Changes in MRI images compared to the baseline imaging.Correlations between dosimetry, cognitive decay and MRI abnormalities onset after RT.

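### The only method assigned to the biomarkers tests change after radiotherapy, so the stated objective, their link with cognitive impairment, is left without a test

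*Protocol article*

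**What the plan says.** **Aim.** Objectives (Protocol article) includes a secondary objective for the markers: "to evaluate the correlations between cognitive impairments and biological abnormalities". Background looks for markers "which could be accurate for the screening of patients at risk of cognitive impairments", and Discussion says that several will be tested "in order to try to individualize prognostic biomarkers of leukoencephalopathy". The Abstract and the opening paragraph of Planned analysis both announce that marker data will be related to cognitive impairment.

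**Endpoint.** In Study endpoints, the biomarker endpoint is the difference in "concentration between the measurements before RT and: at the end of the RT, RT + 4 weeks, RT + 12 months and RT + 36 months". Cognitive status plays no part in it. A separate endpoint covers correlations: "Correlations between dosimetry, cognitive decay and MRI abnormalities onset after RT". Biomarkers are not in that list.

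**Analysis.** Planned analysis lists general methods (analysis of variance, chi-square or Fisher tests, two-sided 5% level) and then says "Details of the analyzes are shown below". In Analysis of evaluation criteria, changes in the markers between the pre-radiotherapy, 4-week, 12-month and 36-month measurements "will be analyzed by parametric distribution comparison tests (Z) or nonparametric if needed (Wilcoxon tests". The Cox model in the same section has organ dose as its exposure, adjusted for risk factors, and biomarkers are not mentioned.

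**The concern.** A change test and an association test address different hypotheses. The first asks whether the average concentration differs between two times. The second asks whether patients who decline cognitively have different levels, or different changes, from patients who do not. Only the second bears on correlation with impairment, on screening or on prognosis.

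The protocol appears to treat the first as an answer to the second. The biomarker paragraph under Procedures notes that the markers may predict cognitive impairment and concludes that their course after irradiation will therefore be analysed. Study endpoints and Analysis of evaluation criteria follow the same line.

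At stake is one named secondary objective. If only the assigned test is run, the report can say which markers move after radiotherapy but not which are related to decline.

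**Working it through.** **1. The passages side by side**

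| Axis | Stated aim | Method assigned in Analysis of evaluation criteria | Linked to cognitive outcome? |
|---|---|---|---|
| Dosimetry | relation with cognitive decline | Cox model, adjusted for risk factors | yes |
| CSCT | detection of impairment | sensitivity and specificity against the formal assessment | yes |
| Biomarkers | correlation with impairment, prognosis | Z or Wilcoxon tests between measurement times | none stated |

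The article thus names an outcome-linked method for two axes. For the third it names a method that addresses another question.

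**2. The plan's own figure.** The only sample-size figure, 246 to 384, concerns the incidence proportion. With n = 1.96² × P(1 − P) / d² and d = 0.05 (not stated, inferred because it fits):
- P = 0.2: 3.8415 × 0.16 / 0.0025 = 245.9
- P = 0.5: 3.8415 × 0.25 / 0.0025 = 384.1

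It reproduces and is not affected by this point. No figure is given for the biomarker objective.

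**3. How far apart the two questions are.** Inputs from the protocol: two-sided alpha 5% (Planned analysis), impaired share π from 0.2 to 0.5 and 400 inclusions (Sample size consideration). Assumed: normally distributed changes with SD 1, and these two markers:
- Marker A rises 0.3 SD in everyone, with no link to impairment.
- Marker B changes by +0.5(1 − π) SD in impaired and −0.5π SD in unimpaired patients. The groups differ by 0.5 SD, and the cohort mean is π × 0.5(1 − π) − (1 − π) × 0.5π = 0.

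Normal approximations:
- Before-after, marker A: z = 0.3 × √n. For n = 400, z = 6 (power about 100%). For n = 100, z = 3 (power Φ(3 − 1.96) = 0.85).
- Impaired versus unimpaired, marker B: z = 0.5 / √(1/(nπ) + 1/(n(1 − π))). For n = 400 and π = 0.2, z = 0.5 / 0.125 = 4 (power Φ(2.04) = 0.98). For n = 100 and π = 0.2, z = 0.5 / 0.25 = 2 (power Φ(0.04) = 0.52).

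Simulation (1000 runs per setting; signed-rank on the pooled change, rank-sum between groups; range over π = 0.2, 0.3, 0.5), share of runs significant:

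| n | A, before-after | A, by impairment | B, before-after | B, by impairment |
|---|---|---|---|---|
| 400 | 100% | 4.3–6.1% | 4.2–4.9% | 97.8–99.8% |
| 200 | 98.0–98.9% | 4.7–5.9% | 4.5–4.7% | 77.4–92.0% |
| 100 | 81.2–84.8% | 3.9–4.7% | 4.3–5.0% | 48.9–69.2% |

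**4. Numbers likely to be available.** Discussion puts median survival below 18 months. Assuming exponential survival with a median of exactly 18 months, 400 × 0.5^(12/18) = 252 are alive at 12 months and 400 × 0.5² = 100 at 36 months, before other losses. With 80% power, the detectable difference in marker change between impaired and unimpaired patients is (1.96 + 0.84) × √(1/(nπ) + 1/(n(1 − π))). For π from 0.2 to 0.5 this is 0.35 to 0.28 SD with 400 evaluable patients, 0.49 to 0.40 SD with 200, and 0.70 to 0.56 SD with 100. Early samples therefore carry the most information.

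**5. Multiplicity.** Table 4 lists 3 classical markers, 12 microRNAs and microparticles, about 16 in all. One test each at 5% gives 16 × 0.05 = 0.8 expected false positives if none is related to decline.

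**The case against.** The strongest reply is that the link is announced, in the Abstract, in Objectives and in Planned analysis, and that a condensed article may leave the model to the full protocol or the SAP. The general methods include analysis of variance, which could compare marker levels by cognitive status. Biomarkers might also be meant among the risk factors in the Cox model. This part stands: the association analysis is intended, and a reader who inferred that it is not planned would go too far. But the text assigns neither analysis of variance nor the Cox adjustment to this use. The biomarker method it does assign matches an endpoint and a line of reasoning about change over time, so this is a stated choice and not only missing detail.

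Three stronger readings are tempting and not supported:
- That markers will be kept or dropped on the before-after test, so the objective is answered wrongly. No selection rule is given. The objective is left unanswered by that test, which is a lesser fault.
- That the test is declared to be on the whole cohort. This is inferred: no grouping is stated, and none is excluded. The stated contrast is between times.
- That 12-month samples cannot predict. Formal assessment is yearly and follow-up lasts 3 years, so a 12-month value precedes decline first found later. Concurrent values are also legitimate for a correlation.

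The illustration is built to separate the two hypotheses. Marker B has a zero mean by construction, so 5% on the before-after test is inevitable. It shows that the tests answer different questions and does not measure harm in this study.

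**Conclusion.** The point holds as a mismatch between objective, endpoint and assigned analysis. A biomarker–cognition analysis is announced, but the only method tied to the biomarkers tests change between measurement times, and such a test carries no information on association with decline. As specified, the secondary biomarker objective is unanswered. The primary incidence estimate and its sample size are untouched.

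The mismatch rests on the text alone. The simulated percentages rest on assumed effect sizes, normal changes and the protocol's range of 0.2 to 0.5 for the impaired share. The counts of survivors rest on an assumed exponential curve and are optimistic, since the stated median is below 18 months. The change should be made, because it is cheap and uses data already being collected.

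A smaller inconsistency belongs with it: Study endpoints lists a sample at the end of radiotherapy that neither the biomarker paragraph under Procedures nor Analysis of evaluation criteria mentions.

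**What to change.** - **Study endpoints:** add biomarkers to the correlation endpoint.
- **Analysis of evaluation criteria:** add an outcome-linked biomarker analysis. One workable form is a cause-specific Cox model for time to cognitive impairment from a landmark at 4 weeks after radiotherapy. Its covariates would be each marker's baseline level and its change from baseline to 4 weeks, adjusted for the same risk factors and organ dose as the dose–response model. Other outcome-linked models would also serve.
- **Death and recurrence:** state how each is handled, as a competing event or as censoring. Death will be common, and the primary endpoint applies after local recurrence is excluded.
- **Multiplicity:** name a control across the roughly 16 markers.
- **Later samples:** use 12-month values as concurrent correlates, or as predictors only of later decline in patients still event-free at 12 months. Use 36-month values as concurrent correlates only.
- **Before-after tests:** keep them, labelled as description of marker change.
- **Sampling times:** reconcile the end-of-radiotherapy measurement across Study endpoints, Procedures and Analysis of evaluation criteria.

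The cost is protocol or SAP wording and one extra model per marker, with no new data. Patients with an event or death before the landmark leave this one analysis, and multiplicity control will cost some power for each marker.

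### The Objectives ask for CSCT sensitivity and specificity for follow-up decrement, but the stated analysis gives specificity only to the pre-radiotherapy comparison

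*Protocol article*

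**What the plan says.** The last secondary objective in the Objectives section is "the assessment of the sensibility and specificity of a quick cognitive test", the CSCT, and its target is "to detect a cognitive decrement during the follow up of the patients". Two accuracy measures are named, and the condition to be detected is a change after treatment.

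The section Analysis of evaluation criteria describes two CSCT analyses. The first is of the "sensitivity and specificity of the CSCT to demonstrate cognitive impairment by comparing the CSCT performed before radiotherapy and detailed neuropsychological assessment (gold standard"), with the formal battery done at the same time. The second compares CSCT decay over the follow-up years with the formal assessment, "to study its sensibility in detecting cognitive decrement after radiotherapy". Specificity appears in the first and not in the second.

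Two definitions bear on this. Under Procedures, "CSCT decrement is defined as a loss of 1 standard deviation compared to baseline", and it must be seen "during two consecutive assessments". Under Study endpoints, formal decline is a score lower than the patient's "baseline score before radiotherapy for at least 2 cognitive domains", once local recurrence has been excluded.

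Procedures also schedules the formal assessment at baseline and every year after radiotherapy, and brings the next one forward when the CSCT shows a decrement. Table 2 lists the CSCT among the tests of the formal battery.

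**The concern.** The objective and the analysis meant to serve it do not match. The objective needs the proportion of non-declining patients whom the decrement rule correctly leaves unflagged. The only specificity planned answers another question: whether a single CSCT score, taken after surgery and before radiotherapy, separates patients already impaired from those who are not.

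The difference matters because of the intended use. The Background says that the CSCT could "be used as an alarm to start a more extensive formal assessment", and that assessment lasts two hours with a trained neuropsychologist. How often a stable patient would be sent for it unnecessarily depends on specificity during follow-up. A report that followed the plan literally would give a sensitivity for the decrement rule and a specificity for a different classification.

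**Working it through.** **1. The texts side by side.**

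| Place | Measure named | Target | Time |
|---|---|---|---|
| Objectives | sensitivity and specificity | decrement | follow-up |
| Analysis of evaluation criteria, first CSCT sentence | sensitivity and specificity | impairment | before radiotherapy |
| Analysis of evaluation criteria, second CSCT sentence | sensibility only | decrement | after radiotherapy |
| Procedures | sensibility only | impairments | baseline and follow-up |
| Abstract | sensibility only | leukoencephalopathy decrement | not stated |

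No section plans specificity for follow-up decrement.

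**2. Whether the baseline figure can substitute.** The decrement rule and the formal decline definition both compare a later score with the patient's own baseline. The baseline analysis classifies a level at one time point. The two specificities have different index rules, different references and different sets of unaffected patients, so neither can be derived from the other.

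**3. The plan's own figure.** The article gives no number for CSCT accuracy. Its sample size of 246 to 384 concerns the incidence estimate. It reproduces with n = 1.96² × P(1−P)/d² if the unstated half-width d is taken as 0.05: P = 0.2 gives 245.9 and P = 0.5 gives 384.2. Only the range P = 0.2 to 0.5 is carried into the illustration below.

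**4. What specificity decides.** The share of positive results that are correct is PPV = Se·P / [Se·P + (1−Sp)(1−P)]. Sensitivity Se = 0.80 and the specificities are assumed.

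- P = 0.2, Sp = 0.95: 0.16/(0.16 + 0.04) = 80%
- P = 0.2, Sp = 0.85: 0.16/(0.16 + 0.12) = 57%
- P = 0.2, Sp = 0.70: 0.16/(0.16 + 0.24) = 40%
- P = 0.5, Sp = 0.95: 0.40/(0.40 + 0.025) = 94%
- P = 0.5, Sp = 0.85: 0.40/(0.40 + 0.075) = 84%
- P = 0.5, Sp = 0.70: 0.40/(0.40 + 0.15) = 73%

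**5. Could the false-positive rate be taken as negligible?** A simulation of 200,000 stable patients applied the rule at quarterly visits. It assumed normal scores, no practice effect, the SD read as the between-patient SD, and test-retest correlation r. The share ever meeting the rule over 12 visits (three years) was 19.7% at r = 0.6, 14.2% at 0.7, 7.6% at 0.8 and 1.2% at 0.9. It therefore depends on a reliability that has to be learned in this population.

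**6. Whether follow-up specificity would be estimable.** The half-width is 1.96·√[Sp(1−Sp)/m], with m patients who have not declined. Assume 100 to 400 evaluable patients and a decline proportion of 0.2 to 0.5, so that m runs from 50 to 320.

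- m = 320, Sp = 0.9: ±3.3 percentage points
- m = 50, Sp = 0.7: ±12.7 percentage points

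Usable precision is within reach across much of that range.

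**The case against.** The strongest reply is that the article uses sensibility loosely. Procedures applies the word to the CSCT comparison at baseline as well as during follow-up, and the analysis section calls that same baseline comparison sensitivity and specificity. The omission at follow-up may be shorthand. This has force, and it makes the point one of unclear commitment rather than a proven decision to drop specificity. It does not remove the mismatch: the Objectives name the two measures separately, and the analysis section names specificity in one CSCT sentence and leaves it out of the next.

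A reader might infer that the baseline table cannot be constructed, because a loss from baseline cannot occur at baseline. The documents do not support this. The baseline sentence concerns impairment, not decrement, and the same section speaks of patients already impaired before radiotherapy, so a level-based classification is intended. Its unstated cut-off is detail that an article ordinarily leaves to the full protocol or SAP.

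A reader might also infer that follow-up specificity can never be obtained. That fails too: formal assessments are yearly whatever the CSCT shows, so CSCT-negative patients also receive the reference assessment.

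It is also fair to say that the alarm is Background wording about a possible use, not the wording of the objective, and that nothing states that the baseline specificity will be presented as that of the decrement rule.

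**Conclusion.** The point holds in a limited form. The stated analysis does not commit to the follow-up specificity that the objective requires, and the baseline specificity cannot replace it. It affects one secondary objective. The primary incidence estimate and the data collection are untouched.

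The conclusion rests on comparing the sections and needs no numerical assumption. The predictive values, the simulated false-positive rates and the precision figures only show why specificity matters. They rest on assumed sensitivity, specificity, test-retest correlation and evaluable numbers. The range 0.2 to 0.5 is the protocol's expected proportion with complications in the cohort, borrowed here for the proportion declined at the time of classification.

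**What to change.** In Analysis of evaluation criteria, reword the follow-up sentence to say that the comparison estimates both sensitivity and specificity, with 95% confidence intervals, of the CSCT decrement rule in Procedures against formal decline from baseline in two or more domains as in Study endpoints. Say that the yearly formal assessments, including those of CSCT-negative patients, supply the reference.

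Two conditions belong in the same paragraph:

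- Leave the CSCT out of the reference classification. Table 2 places it in the formal battery, and a reference that contains the index test would favour agreement.
- State how assessments brought forward by a positive CSCT are handled. CSCT-positive patients are otherwise verified earlier than CSCT-negative ones, which can distort both measures.

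Report the baseline comparison as a separate cross-sectional analysis of impairment.

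The cost is analysis wording and a little extra analysis. No visit or test is added, since the assessments are already scheduled.
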